#### Analysis to Balance the Exposed and Referent Groups in Each Cohort

Propensity scores will be calculated using multivariable logistic regression, incorporating more than 400 baseline characteristics (the complete list and coding definitions are provided in Multimedia Appendix 2). Characteristics include calendar year, prior use of drug A, demographics (eg, age, sex, neighborhood income quintile, urban vs rural residence, geographic region [31], and long-term care home residency), comorbidities (eg, asthma, diabetes, coronary artery disease) assessed over the 5 years before cohort entry, health care use in the year prior (eg, hospitalizations, emergency room visits, specialist consultations), and prescription drug dispensing within 120 days before cohort entry. The 120-day lookback period accounts for potential delays in prescription refills, ensuring comprehensive capture of medication dispensing.

The propensity scores will estimate the probability of a patient being in the exposed group versus the referent group, given their baseline characteristics. To enhance the comparability of the exposed and referent groups, we will exclude (1) individuals in the referent group with propensity scores lower than the lowest 1% of scores in the exposed group and (2) individuals in the exposed group with propensity scores higher than the highest 99% of scores in the referent group. This will also ensure that we do not violate the positivity assumption in causal inference, which requires that there should be a nonnull probability across each stratum of baseline characteristics within both the exposed and referent groups [32].

Inverse probability of treatment weighting (IPTW) using average treatment-effect-in-the-treated (ATT) weights will then be used to balance the exposed and referent groups on baseline characteristics as follows: Individuals in the referent group will be weighted using ATT weights, defined as their odds of being in the exposed group (propensity score/[1 − propensity score]). Individuals in the exposed group (the medication pair group) will receive weights of 1. This method will produce a weighted pseudosample of individuals in the referent group with a distribution of measured characteristics similar to that of the exposed group [33,34]. Between-group differences in baseline characteristics in the weighted samples will be examined using standardized differences (SDs) [35].

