Survival analysis. To assess whether the initial signal persists when analyzed using a time-to-event approach, we will conduct a Cox proportional hazards regression with a 30-day follow-up period, censoring on death when all-cause mortality is not the outcome of interest. We will test the proportional hazards assumption by including an interaction term between the new-user status and follow-up time. This analysis will help determine whether the signal is robust across different modeling techniques.Negative-control exposure analyses. To detect potential biases from unobserved confounders, we will perform negative-control exposure analyses. A negative-control exposure is a variable that shares the same sources of bias as the drug of interest but cannot plausibly cause the outcome. We will rerun the regression analyses for the initial signals using a control exposure period starting 90 days before cohort entry [37]. This analysis will help identify any confounding factors that may have influenced the initial signal. Notably, the outcome of all-cause mortality cannot be examined with this method, as all patients lived to their cohort entry date. A positive association (ie, RRs and RDs significantly different from null, with *P*<.05) in this analysis would suggest potential confounding, whereas the absence of an association would bolster the credibility of the original signal.E-value analysis. We will conduct E-value analyses to quantify the minimum strength of association an unmeasured confounder would need to have with both the drug combination and the outcome to negate the observed signal [38]. Larger E-values indicate that substantial unmeasured confounding would be required to explain away the signal, whereas smaller E-values suggest that minimal unmeasured confounding could do so. For an initial signal to be considered robust, the E-value must exceed 2.Propensity score matching. To further validate the robustness of the signal, we will use 1:1 propensity score matching to balance the exposed and referent groups on baseline characteristics [39]. This method estimates the average treatment effect in the treated and mitigates the influence of extreme weights, which can occur with IPTW. Consistency between the results of this analysis and the initial findings will strengthen the validity of the signal.Bootstrap analysis. We will use a multiplier bootstrap procedure to compute RRs and RDs across 200 random samples, each of the same size as the original cohort. This method helps correct SEs and CIs, ensuring they have the correct coverage rates [36,40]. For the signal to be considered robust, at least 90% of the bootstrap samples must yield results consistent with the original findings, with *P*<.05 and CIs for RRs and RDs in the same direction as initially observed.

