### Challenges and Limitations

Despite using advanced statistical techniques to control for confounding, residual confounding may still be present [51]. Factors that are not captured in the administrative data or that are measured with error could bias our results [52]. To address this, we will conduct multiple sensitivity analyses and use negative control outcomes to assess the robustness of our findings [37].

Our study focuses on acute (30-day) outcomes, which will not capture the effect of long-term exposure [53]; however, we will conduct additional analyses to assess longer follow-up times.

The study is designed to identify harmful DDIs with a moderate-to-high risk in magnitude in cohorts of at least 1000 individuals, and therefore, it will have limited statistical power to detect small risk increases.

Our study does not include data on nonprescription (over-the-counter) drugs, drugs prescribed in hospitals, or comprehensive outpatient prescription drug use in children or adults aged under 65 years. These exclusions may limit the generalizability of our findings to a broader population. However, the focus on older adults is justified, given their higher risk of polypharmacy and adverse drug interactions.

Given the large number of comparisons being made, there is a risk of spurious findings due to multiple testing [16]. To mitigate this, we will apply the Benjamini-Hochberg procedure to control the false discovery rate and use E-values to assess the robustness of our findings against unmeasured confounding [31].

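### The negative-control period lies inside the propensity-score look-backs, so a null control result is weak evidence against unmeasured confounding

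*Protocol article*

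**What the plan says.** Under the heading on sensitivity and bias analyses, the Protocol article introduces a negative-control exposure analysis whose stated aim is to detect bias from unobserved confounders. The instruction is: "We will rerun the regression analyses for the initial signals using a control exposure period starting 90 days before cohort entry". A significant RR and risk difference (RD) at P<.05 is read as a sign of confounding, "whereas the absence of an association would bolster the credibility of the original signal". The length of the control period is not given. The article itself notes that all-cause mortality cannot be examined in this way.

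The section on balancing the groups anchors the propensity-score covariates at cohort entry:
- The longest window is for diagnoses: "comorbidities (eg, asthma, diabetes, coronary artery disease) assessed over the 5 years before cohort entry".
- The shortest window is for medicines: "prescription drug dispensing within 120 days before cohort entry".
- Between them lies a one-year window for use of services: "health care use in the year prior (eg, hospitalizations, emergency room visits, specialist consultations".

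The weights follow from that score: "Individuals in the referent group will be weighted using ATT weights, defined as their odds of being in the exposed group".

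Support in the sensitivity and bias analyses is part of step 1 of the signal framework. The Limitations section describes the check differently: "we will conduct multiple sensitivity analyses and use negative control outcomes to assess the robustness of our findings". The Abstract also speaks of negative control outcomes.

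**The concern.** Neither group takes drug B in the control period, because anyone dispensed it in the 180 days before entry is excluded. A difference between the groups in that period should therefore reveal confounding. This works only if the comparison has not already been adjusted for what happened in the period. Here the score includes history running through the period up to entry, so the control outcome is partly adjusted for itself, while unmeasured confounding after entry remains.

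At stake is how a null is read. The referent group is users of drug A without drug B, so confounding by the reason for starting B is a central threat. Propensity-score matching draws on the same measured characteristics. The Cox and bootstrap analyses vary the model and the standard errors, and the E-value describes how much confounding would be needed without looking for it. The control period is the planned sensitivity analysis that looks for it in the data.

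**Working it through.** **1. Compare the windows.** The control period starts at day -90. The look-backs reach 120 days, 1 year (365 days) and 5 years (5 × 365 = 1,825 days) before entry. Since 90 < 120 < 365 < 1,825, every day from -90 to entry lies inside all three.

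**2. Is the score re-estimated?** The instruction is to rerun the regressions. The same wording is used for the 7-, 14-, 60- and 90-day follow-up analyses, where only the outcome window changes. Balancing is a separate step under its own heading and is not said to be repeated. The remark that all patients lived to cohort entry also keeps the cohort tied to its entry date. The plain reading is that the existing weights are used.

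**3. What the weights do to a control-period event.** Take the extreme case, in which the event itself is the covariate. Let n1 exposed and n0 referent people have the event, and m1 and m0 not have it. The referent weights (odds of exposure) are n1/n0 and m1/m0. The weighted referent risk is

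n0(n1/n0) / [n0(n1/n0) + m0(m1/m0)] = n1/(n1 + m1),

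which is the exposed risk. The control RR is exactly 1, however strong the confounding. When the event only contributes to a broader covariate, the pull is weaker.

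**4. Size under assumed confounding.** The plan gives no figure to reproduce. The simulations use its estimator (logistic score, weights for the effect in the treated, weighted RR) with a true RR of 1. The control period is taken as days -90 to -61, an assumption that reuses the 30-day outcome window. The unmeasured confounder has log effects of 0.9 per SD on exposure and on outcome (300,000 people, 4 replicates; 600,000 and 6 for the last row). Ranges cover any-event and count covariates.

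| History in the score | Follow-up RR (pure bias) | Control RR, weights as written | Control RR, look-backs ending before day -90 |
|---|---|---|---|
| Own outcome, 120 days, 30-day risk 0.5% or 2% | 1.85–2.03 | 0.97–1.06 | 1.97–2.14 |
| Own outcome, 1 year, 0.5% or 2% | 1.65–2.06 | 0.97–1.17 | 1.76–1.95 |
| Own outcome, 5-year any-event flag, 0.5% or 2% | 1.74–1.83 | 1.18–1.43 | 1.71–1.78 |
| Own outcome, 1 year, half-persistent confounder, 1% | 1.92–1.97 | 1.01–1.02 | 1.35–1.38 |
| Cause-specific outcome; 1-year all-cause hospitalization count only | 1.85 | 1.08 | 2.00 |

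The 5-year count gave 1.51, 0.98 and 1.67 at 0.5% risk. At 2% risk it gave unusable weights (follow-up RR 0.61) and is set aside.

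A second set (400,000 people, 4 replicates, outcome risk 0.2–0.5% per month, other admissions at an assumed 3–10% per month) put only 1-year all-cause hospitalization in the score:
- Confounder unrelated to other admissions: follow-up RR 1.95–2.16, control RR 1.73–2.01.
- Confounder moderately related (0.4 per SD): follow-up RR 1.91–2.06, control RR 1.31–1.59.
- For comparison, own event history in the score: control RR 0.95–1.00.

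A third set (400,000 people, 6 replicates, log effects 0.8 or 1.0 per SD, 30-day risk 0.3–3%, own event history in the score) gave follow-up RR 1.43–2.05, control RR 0.99–1.01, and 1.43–2.18 with re-anchored covariates.

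**The case against.** The strongest reply is that masking depends on what is in the score. The article gives examples from more than 400 characteristics and leaves the list to an appendix not shown. Many of the 74 outcomes are specific, such as Achilles tendon rupture or hyponatremia, and may have no covariate of their own. This stands. A reader might infer that the control reads null whether or not confounding exists. The documents do not support that: the near-exact nulls come mostly from putting the outcome's own history in the score, and the other settings show anything from near-complete masking (1.08) to almost none (2.01).

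A second reply is that a fuller document may re-anchor the covariates. That is possible, since this is a condensed article, but its wording points the other way and one sentence would settle it.

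Third, a positive control result still counts against a signal, the article compares both initiation orders, and later steps require external evidence and two reviewers. So it would be too strong to say that a null certifies a biased signal as credible.

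Two further inferences fail. All-cause mortality is not left without any check: the E-value, Cox, matching and bootstrap analyses still apply. The P<.05 rule is not an error in itself. Every test depends on sample size, and dividing the signal RR by the control RR is a debatable preference that assumes constant bias over time.

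**Conclusion.** The point holds in a bounded form. The overlap is a fact of the text. On the plain reading that the weights are not refitted, control-period events feed the balanced covariates and the control RR is pulled towards 1. The pull is nearly complete for outcomes that are or feed covariates, with any hospital admission and any emergency visit the clear cases, and partial or slight for outcomes weakly represented in the score. For the first kind, a null says almost nothing about unmeasured confounding, yet the plan counts it in the signal's favor.

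The simulated magnitudes show direction and rough size only. They rest on assumed confounder strength, an assumed 30-day control period and an unseen covariate list. The mismatch between negative control outcomes (Abstract, Limitations) and a negative-control exposure (Methods) is a matter of wording.

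**What to change.** For this analysis:
- Re-measure the covariates and re-estimate the score and weights with every look-back (5-year, 1-year, 120-day) ending before day -90.
- State the length of the control period.
- Report the control-period RR and RD with confidence intervals.
- Do not read a non-significant result by itself as strengthening the signal. Even with re-anchored covariates, a half-persistent confounder showed only 1.35–1.38 of a 1.92–1.97 bias.
- Align the Abstract and Limitations with the negative-control exposure analysis in the Methods.

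The cost is some wording and one extra propensity-score fit per signal, with a slightly shorter covariate history where a look-back cannot be moved back in full. Moving the windows is better than cutting them: cutting would leave 120 - 90 = 30 days of dispensing. Moving the dispensing window reaches back 90 + 120 = 210 days, within the year of prior drug coverage that the age criterion secures.

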#### Criteria for Identifying Potential Signals of Harmful DDIs

Associations between a drug pair and an adverse outcome that meet the following criteria will be considered potential signals of harm and analyzed further:

Thresholds for RRs and RDs. The lower bound of the 95% CI for the RR must be ≥1.33, and for the RD, it must be ≥0.1%. These thresholds were chosen to ensure that only clinically significant increases in risk (of sufficient magnitude to be of concern) are considered. This analysis will focus solely on potential harms from drug combinations rather than protective benefits.Statistical significance. The *P* values from the modified Poisson regression model (for RRs) and the binomial regression model (for RDs) must be statistically significant after applying the Benjamini-Hochberg correction. This correction accounts for multiple comparisons across all outcomes and drug pair cohorts. The false discovery rate will be set at 5%, and the highest *P* value below the Benjamini-Hochberg critical value will be considered statistically significant, along with all *P* values below it. This correction will minimize the risk of false-positive discoveries (type I errors).

Drug pair cohorts that do not generate significant signals will not undergo further analysis.

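### The bootstrap pass rule counts samples with P<.05 against the null, so no bootstrap-corrected CI is tested against the plan's own bounds of RR 1.33 and RD 0.1%

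*Protocol article*

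**What the plan says.** Under Criteria for Identifying Potential Signals of Harmful DDIs, a signal is defined by confidence limits: "The lower bound of the 95% CI for the RR must be ≥1.33, and for the RD, it must be ≥0.1" per cent. P values for RR and RD must also survive Benjamini-Hochberg. "The false discovery rate will be set at 5" per cent, and "This correction accounts for multiple comparisons across all outcomes and drug pair cohorts".

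Under Sensitivity and Bias Analyses to Guard Against Spurious Discoveries, the plan adds a bootstrap: "We will use a multiplier bootstrap procedure to compute RRs and RDs across 200 random samples". Its purpose is given as "This method helps correct SEs and CIs, ensuring they have the correct coverage rates". The pass rule follows at once: "For the signal to be considered robust, at least 90% of the bootstrap samples must yield results consistent with the original findings". A sample counts as consistent when it is significant at the 5% level and its RR and RD intervals lie on the same side of the null as in the main analysis.

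The rule affects the outcome, because Step 1 of the Overall Framework requires support in the sensitivity and bias analyses before a signal goes forward.

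**The concern.** The purpose and the rule do not match. A signal is defined by two lower bounds, and both depend directly on the SE. If the bootstrap is there because the model SE may be wrong, the natural use is to recompute those bounds and see whether they still reach 1.33 and 0.1%. The stated rule instead asks how often a sample is significant against no effect, and sends no corrected SE, CI or P value back to the signal criteria.

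Two errors are possible. A signal whose corrected bound misses the threshold can be labelled robust. A sparse signal that met every declared criterion can be dropped by a P cut that the plan never states.

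**Working it through.** The plan gives no error rate or power for this rule, so there is no figure of its own to reproduce.

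**Inputs from the protocol:** 200 samples; pass share 90%; P<.05 per sample for RR and RD; bounds 1.33 and 0.1%; FDR 5%; at least six events per group; about 200,000 drug pairs and up to 74 outcomes; median 583 new users per initial cohort.

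**Assumptions:** two-sided P; each sample's P uses the model's own SE; normal approximation; SE(log RR) of about √(1/d₁ + 1/d₀), with d₁ and d₀ the exposed and referent events.

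**1. Implied cut when the model SE is right.** Bootstrap estimates centre on the observed one, so the expected share with P<.05 is Φ(z − 1.96). Setting this to 0.90 gives z = 1.96 + 1.28 = 3.24, two-sided P = 0.0012. With only 200 samples the cut is blurred: the chance of passing is 5% at P = 0.0024, 50% at P = 0.0013 and 95% at P = 0.0006.

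**2. Against Benjamini-Hochberg.** Its cut is 0.05 × (share of tests rejected), and 0.0012/0.05 = 2.4%. Chance that a signal exactly at the Benjamini-Hochberg margin passes the bootstrap:

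| Share rejected | P cut | z | Chance of passing |
|---|---|---|---|
| 0.1% | 0.00005 | 4.06 | about 100% |
| 1% | 0.0005 | 3.48 | 98% |
| 2.4% | 0.0012 | 3.24 | 55% |
| 5% | 0.0025 | 3.02 | 4% |
| 10% | 0.005 | 2.81 | <0.1% |

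**3. Against the CI bounds alone.**
- RR: a lower bound of 1.33 guarantees z ≥ 1.96 + ln(1.33)/SE. This reaches 3.24 only if SE ≤ 0.285/1.28 = 0.223, about 40 events in each group (2/0.223²), or about 20 exposed events with a very large referent group (1/0.223²).
- Six events per group: SE = √(2/6) = 0.577, z = 1.96 + 0.285/0.577 = 2.45, expected share 69%.
- RD: a lower bound of 0.1% guarantees z = 3.24 only if SE(RD) ≤ 0.1/1.28 = 0.078 percentage points.

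A multiplier-bootstrap simulation (exponential weights, RR and RD jointly, assumed 1:5 exposed to referent, no confounding) agrees. With the CI bounds alone, every signal passed at 10,000 exposed. At 583 exposed and 2% risk, 27%, 51% and 93% passed for RR 1.5, 2 and 3. Adding Benjamini-Hochberg at 2.4% rejected or less, 99–100% passed wherever there were enough signals to estimate.

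**4. When the model SE is too small.** Take true SE(log RR) = 0.10 and an assumed true-to-reported ratio of 1.3, so the reported SE is 0.10/1.3 = 0.0769 (23% too small).
- Reported lower bound 1.33: log RR = 0.285 + 1.96 × 0.0769 = 0.436, RR 1.55.
- Reported z = 0.436/0.0769 = 5.67.
- Share with RR P<.05: Φ((5.67 − 1.96)/1.3) = 99.8%.
- RD with a large referent group: z ≈ (1 − 1/1.546)/0.0769 = 4.59, share Φ((4.59 − 1.96)/1.3) ≈ 98%.
- Correct RR lower bound: exp(0.436 − 0.196) = 1.27.

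The signal clears the 90% count on both measures while its corrected RR bound is below 1.33.

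**5. Drift of the rule.** With ratio k, a signal passes at true z = 1.96/k + 1.28. At k = 1.5 this is 2.59 (true P = 0.0096); at k = 2 it is 2.26 (true P = 0.024). The effective cut loosens as the SE gets worse.

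**The case against.** **The rule is not blind to the SE.** This stands: the share depends on the bootstrap spread, and at k = 1.5 the required model z rises from 3.24 to 1.96 + 1.5 × 1.28 = 3.88. A reader might infer that the step merely repeats a p-value cut; that goes too far. But signals at the 1.33 bound with small SEs clear 3.88 easily, and the thresholds are still not rechecked.

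**Redundancy is conditional.** A reader might infer that most signals have passed before the bootstrap starts, or that about 21 exposed events guarantee a pass. The documents support neither. The Benjamini-Hochberg rejection share is not given. The 21-event figure uses RR alone with an effectively infinite referent group. At an assumed exposed risk of 4%, SE = √(0.96/21) = 0.214, the RR at the bound is 2.02, and the RD z is (1 − 1/2.02)/0.214 = 2.36, so only about 66% of samples reach RD P<.05 and the signal fails. An expected share of exactly 90% is also close to a coin flip with 200 samples.

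**Other safeguards exist.** Propensity score trimming, 1:1 matching and the later evidence review all help, and the plan itself says matching mitigates extreme weights. None of them applies a bootstrap-corrected CI to 1.33 or 0.1%.

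**The article is condensed.** Whether propensity scores are re-estimated in each sample may fairly be left to a fuller plan, and its absence is not the point. The pass share, the per-sample criterion and the number of samples are all stated here, and the sentence itself spells out consistency as significance and direction.

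**Conclusion.** The point holds, with moderate weight. The stated rule does not carry out the correction it is credited with: it tests significance against the null and leaves the two signal-defining bounds unchecked. With a correct SE it acts as a P cut near 0.0012, largely redundant in well-populated cohorts or at a Benjamini-Hochberg rejection share up to about 2.4%, and able to remove sparse signals otherwise.

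In the worked case a reported RR bound of 1.33 is really 1.27 and still passes. That rests on the assumed ratio of 1.3 and the normal approximation. A reader might infer from it that the planned SEs are too small, or that spurious associations get through. The documents show neither: the size and direction of any SE error are unknown, and the example has a true z of 0.436/0.10 = 4.36, so it is a missed threshold on a clearly non-null association.

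**What to change.** Within each planned bootstrap sample, re-estimate the propensity score, the trimming and the weights. Take the bootstrap SD of log RR and of RD, rebuild the 95% CIs around the original estimates, and require the lower bounds still to reach 1.33 and 0.1%. Let this check replace the 90% count. If an additional P cut is wanted for sparse signals, declare it openly among the signal criteria.

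The cost is extra computing, confined to associations already flagged as signals, since the 200 samples are planned anyway. Some borderline signals may change status.
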